### Who will be included in each analysis {27b}

The primary analysis will be based on an intention-to-treat approach, including all randomized individuals. Secondary analysis will be based on a per-protocol population. Each oral device contains an integrated sensor that records training frequency, providing objective data to form the per-protocol population. Specific criteria for adherence to the intervention protocol will be specified in the statistical analysis plan. Possible confounders for the per-protocol analysis will be identified using a Directed Acyclic Graph in the statistical analysis plan (SAP), along with a definition of the per-protocol population.

### How missing data will be handled in the analysis {27c}

We will distinguish between informative and non-informative missing data for the primary outcome (DOSS).

Informative missingness: If a DOSS score is missing, a blinded investigator will assess whether the absence is caused by severe swallowing dysfunction or frailty preventing the examination. In such cases, a DOSS value of 0 (worst outcome) will be imputed, in accordance with a composite variable strategy [22]. This assessment will be based on the following criteria: a clinical swallowing examination where a Function Oral Intake Scale score of 1 is achieved [32]. To preserve the investigator’s blindness during this assessment, participants will be strictly instructed not to reveal their group allocation.

Remaining missing values will be imputed using Multivariate Imputation by Chained Equation, conditioned on patients’ baseline variables deemed to possibly be involved in a missing at random mechanism. These will be specified in the SAP.

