### Outcomes {16}

#### Primary outcome

Post-intervention degree of swallowing dysfunction, measured immediately after the completion of the 12-week oral neuromuscular training intervention or use of compensatory strategies (end-of-treatment assessment); examined transnasally with a FEES, assessed using the DOSS [18, 19]. DOSS is an internationally widely used scale for measuring swallowing safety and efficacy on an ordinal scale and is based on the International Classification of Functioning, Disability and Health (ICF) classification. DOSS lists objective criteria on a 7-point Likert scale to systematically rate the functional swallowing severity from 1 (severe dysphagia and total dependency of artificial nutrition) to 7 (normal swallowing function and normal diet) based on symptoms observed during a FEES and impact on eating/drinking function. Subsequently, the DOSS results are directly transferable into recommendations for the patients regarding the diet level (tube feeding, modified diet, or no restriction), independence level (grade of assistance during mealtime), and type of nutrition the patient can swallow safely (liquid, thickened bolus, etc.). The scale has shown high validity and excellent inter- and intra-rater reliability [18, 19]. To account for participants who are too fragile to undergo the FEES examination, a composite variable strategy [22] will be employed to mitigate bias. Specifically, if a DOSS score is missing because a participant is judged to have severe swallowing dysfunction or frailty preventing assessment, a DOSS value of 0 (representing the worst outcome) will be imputed. This procedure is described in greater detail in the section: “Methods in analysis to handle protocol non-adherence and any statistical methods to handle missing data.”

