#### Secondary outcomes

The intervention and the control group will be compared at end-of-treatment and at 6-month follow-up, adjusted for baseline values on the following secondary outcomes:Nutritional status [23] is measured with the Mini Nutritional Assessment Short Form (MNA-SF). The MNA-SF contains 6 items with a total score ranging from 0 to 14; a score of ≥12 points indicate that a person is well-nourished, 8–11 points indicate a risk of malnutrition, and <7 points indicate that the person is malnourished. MNA has been shown to have high sensitivity and specificity (96% and 98%, respectively) and significant agreement between observers (*K* = 0.51) and the MNA-SF has been shown to be a stand-alone nutritional assessment. The total score will be analyzed as an ordinal variable without categorization and compared between group.Swallowing-related quality of life is measured with the Swallowing Quality of Life Questionnaire (SWAL-QOL) [24], which is a patient-reported outcome measure (PROM) and consists of 44 items on a 5-point Likert scale that assesses 10 quality-of-life concepts: burden, eating duration, eating desire, food selection, communication, fear, and mental health. It further contains a dysphagia clinical symptom scale (symptom score). Scores for each domain are calculated using a linear transformation to a total test score ranging from 0 to 100, with higher scores indicating better quality of life. The Swedish version of SWAL-QOL has high internal consistency, high validity, and excellent test-retest reliability. The total score will be treated and analyzed as an ordinal variable without categorization and compared between groups.Rate of aspiration pneumonia based on the modified criteria by Centers for Disease Control and Prevention (CDC) for stroke-associated pneumonia [25]. The data are collected through patient reports and records. The incidence of aspiration pneumonia will be compared between groups.Lip force [26] assessed with a device measuring the lip force in newton (N). The maximum value (best of three trials) will be treated as a continuous variable and compared between groups.Functional status measured with (a) the Barthel index (BI) [27] which is an ordinal scale that consists of 10 items measuring a person’s functional independence on activities in daily living (ADL): bowels, bladder, toileting, bathing, eating, dressing, grooming, transfer, stairs, and ambulation. The scale ranges from 0 to 100. BI is widely used within both stroke care and research, and it is sensitive enough to detect improvement in function after stroke as well as having good reliability between administrators. Functional status is also measured by (b) the modified Rankin Scale (mRS) [28], which is a 7-point scale ranging from 0 (no symptoms) to 6 (death). The mRS has shown high validity and reliability when tested among patients with stroke. BI and mRS total scores will be analyzed as ordinal variables without categorization and compared between groups.Death: The mortality rate will be compared between groups.

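### Death before the 12-week FEES has no place in the DOSS 0 rule; read literally, deaths are imputed by MICE and on average score better than participants too frail for FEES

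*Protocol article*

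**What the plan says.** All references are to the protocol article.

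- **Outcomes {16}, Primary outcome.** The plan adopts a composite strategy for people too fragile for FEES: "if a DOSS score is missing because a participant is judged to have severe swallowing dysfunction or frailty preventing assessment", then "a DOSS value of 0 (representing the worst outcome) will be imputed".
- **Missing data {27c}.** For a missing score, "a blinded investigator will assess whether the absence is caused by severe swallowing dysfunction or frailty preventing the examination". The criterion for that judgement is "a clinical swallowing examination where a Function Oral Intake Scale score of 1 is achieved".
- **Missing data {27c}, the other route.** "Remaining missing values will be imputed using Multivariate Imputation by Chained Equation". The imputation is conditioned on baseline variables. Only the list of those variables is left to the SAP.
- **Analysis population {27b}.** "The primary analysis will be based on an intention-to-treat approach, including all randomized individuals".
- **Secondary outcomes.** "The mortality rate will be compared between groups". Death is also the worst grade, 6, of the modified Rankin Scale (mRS).

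Neither {16} nor {27c} says which DOSS value, or which other strategy, applies to a participant who dies before the end-of-treatment FEES.

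**The concern.** Section {27c} divides every missing 12-week DOSS into two routes. The first needs a live examination, so a death cannot enter it. The second takes whatever remains, and {27b} does not allow deaths to be left out. Followed to the letter, the text gives a dead participant a swallowing score modelled on living ones.

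That defeats the purpose of the composite strategy, which is to count the worst courses as the worst outcome. It also differs from the trial's own mRS, where death is the bottom grade.

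Deaths are foreseeable. Enrolment is 4–12 weeks after stroke, the expected mean age is 75, and the Introduction links dysphagia to early mortality. If the arms differ in mortality, the primary odds ratio would carry little of that difference: excess deaths under training would cost it little, and prevented deaths would earn it little.

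**Working it through.** **1. Inputs.** From Sample size {19}: DOSS 1–7 distribution of 3, 7, 10, 13, 24, 30 and 13%; odds ratio 2; 90% power; 135 subjects (read as per group); 20% dropout; 168 per group. Assumed, because not stated: two-sided alpha of 0.05 and all 12-week death rates.

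**2. The plan's own figure.** The proportional-odds formula behind *popower* is N = 12(z₀.₉₇₅ + z₀.₉₀)² / [(ln OR)²(1 − Σp³)].
- Σp³ = 0.0466, so 1 − Σp³ = 0.9534.
- N = 12 × (1.960 + 1.282)² / (0.6931² × 0.9534) = 275, or 138 per group, against 135 stated.
- Power at 270 is Φ(ln 2 × √V − 1.960), with V = 135 × 135 × 270 / (3 × 271²) × 0.9534 = 21.3. This gives 89.2%, against 90% stated.
- 135 / 0.8 = 168.75, against 168 stated.

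The planning figures reproduce closely. Their distribution has no mass at 0 or for death.

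**3. What an imputed death would look like.** A draw from the planning distribution has mean 0.03×1 + 0.07×2 + 0.10×3 + 0.13×4 + 0.24×5 + 0.30×6 + 0.13×7 = 4.9, and 30% + 13% = 43% of draws fall at DOSS 6–7. These are unconditional values. Conditioning on a poor baseline would probably lower them. The participant too frail for FEES gets 0.

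**4. Effect on the odds ratio.** The planning distribution was split into two arms that differ by an odds ratio of 2 and average back to it (DOSS 5 or below: 65.4% control, 48.6% training). With death rates d_c and d_t, each arm became [d, (1 − d) × survivor distribution], with death as the lowest category. A large-sample proportional-odds model was fitted, with all 168 per arm analysed.

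| Deaths, control v training | Approx. number of 168 | OR, deaths worst (survivor OR 2) | OR, deaths worst (survivor OR 1) |
|---|---|---|---|
| 3% v 6% | 5 v 10 | 1.70 | 0.91 |
| 4% v 8% | 7 v 13 | 1.61 | 0.88 |
| 8% v 4% | 13 v 7 | 2.09 | 1.13 |

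If MICE imputes deaths within arm, the result stays at 2.00 (or 1.00) in every row. If it imputes from the pooled distribution without regard to arm, 3–6% deaths per arm give about 1.96–1.92.

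**5. Price of ranking deaths worst when mortality is equal.**

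| Deaths per arm | OR | Power, 270 analysed | Power, 336 analysed |
|---|---|---|---|
| 0% | 2.00 | 89% | 95% |
| 2% | 1.94 | 87% | 93% |
| 3% | 1.91 | 85% | 92% |
| 5% | 1.86 | 82% | 89% |

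The last column assumes that imputation loses no information.

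**The case against.** **The plan is silent; it does not lay down a rule for death.** A reader might infer that the plan deliberately ranks death above frailty. The documents do not support that. No section says so, and the result follows only from the word for the leftover cases in {27c}. A score that cannot exist after death is arguably not a missing value at all. The frailty wording, or a qualifying examination shortly before death, might bring some deaths under DOSS 0. The SAP may also settle the matter. This decides the wording of the point but does not remove it: {27c} fixes both routes and hands only the imputation variables to the SAP.

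**The ranking holds on average, not in every imputation.** Participants who die probably have worse baselines, and if the zeros enter the imputation model, 0 can itself be drawn. This stands.

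**An odds ratio of 2.0 under MICE presumes imputation within arm.** The plan names only baseline variables. Arm-blind imputation gives about 1.92–1.96, so both figures are needed.

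**The larger shifts need mortality to differ twofold.** A reader might infer that training is expected to raise mortality. Nothing in the documents says so, and the Harms section anticipates no significant adverse events. With equal mortality of 2–5%, the two approaches differ only as 2.00 against 1.94–1.86, and a null effect stays at 1.0. This stands, and it limits the grade.

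**Deaths are not hidden.** They are compared as a secondary outcome and count as mRS 6. That is true, but neither enters the primary odds ratio.

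**Conclusion.** The point holds and should be fixed. As the text reads, a death before the 12-week FEES falls to MICE and receives a DOSS that on average is better than the 0 given to a participant too frail for the examination. This contradicts the composite strategy that the plan chose, and it makes the primary odds ratio largely insensitive to a mortality difference.

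The textual gap is certain; its size is not. The documents give no 12-week mortality. The one-fifth mortality in the Introduction is for stroke in general and cannot be carried over to patients enrolled 1–3 months after onset. Every odds ratio above therefore rests on assumed death rates, an odds ratio of 2 (or 1) in survivors, all 168 per arm analysed, and a stated choice between within-arm and arm-blind imputation.

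**What to change.** - In {16} and {27c}, state that participants who die before the end-of-treatment FEES receive the worst value under the composite strategy, with no clinical examination required. That value may be DOSS 0 or a separate category below it; either removes the inconsistency, and one must be named.
- Restrict MICE to participants known to be alive.
- Apply the same rule at the 75% efficacy look, and count these values in the distribution used for the 50% sample size re-estimation.
- Report a survivors-only analysis as a sensitivity analysis.

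The text change is a sentence or two in the protocol, carried into the SAP, and should be made before the efficacy look. The article lists death among the data collected but does not mention its date. The sponsor should confirm that the date is recorded, since the rule needs to know whether death came before the assessment.

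The statistical cost is dilution by deaths unrelated to training, as set out for equal mortality in step 5 of the working. The re-estimation can take account of it if deaths are counted there.

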### Methods for additional analyses (e.g., subgroup analyses) {27d}

Pre-specified subgroup analyses will be conducted to evaluate the consistency of the treatment effect across key baseline characteristics. The defined subgroups include sex, age group (<65 vs. ≥65 years), stroke type (ischemic vs. hemorrhagic; supratentorial vs. infratentorial), and baseline severity of dysphagia. To assess heterogeneity of the treatment effect, we will fit separate ordinal regression models for each subgroup factor. These models will include an interaction term between the randomized intervention and the subgroup variable. A significant interaction term will indicate a differential treatment effect across the subgroup categories.

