### Characteristics of the people who are needed for the trial

The expected characteristic of the people that will be included in the study is displayed in Table 1.

**Table 1 Tab1:** Expected demographic characteristics of the participants

Characteristic	The people we would expect to see included
Age	Individuals aged 18 years and above; with mean age 75 based on age distribution in the Swedish National Stroke Registry [1]
Sex	Female and male
Gender	Both women and men; with a slightly higher proportion of men, consistent with sex distribution in the Swedish National Stroke Registry [1]
Race, ethnicity, and ancestry	Predominantly individuals of European descent, reflecting the Swedish population; minority representation expected to be low based on national demographics
Socioeconomic status	Participants from varied socioeconomic backgrounds; distribution expected to reflect national patterns, with most in middle-income categories
Geographic location	Nationwide recruitment including rural, suburban, and urban areas across southern, central, and northern Sweden
Other characteristics relevant to the trial	Not applicable

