### Sample size {19}

Expected proportion of patients with dysphagia (i.e., DOSS ≤ 5) at follow-up in the control group is 65% [5]. We have dimensioned our study to detect a marginal odds ratio of 2 when using an ordinal proportional odds model. This corresponds to a proportion of patients with swallowing dysfunction of 52% in the intervention group. We expect a majority of patients to have a DOSS score of 5 or 6 at 12 weeks (end-of-treatment), based on clinical experience. Under the assumption of a marginal DOSS score distribution of 3%, 7%, 10%, 13%, 24%, 30%, and 13% for the DOSS score points of 1–7, respectively, 135 subjects are sufficient to detect an odds ratio of 2 with 90% power using an ordinal proportional odds regression model. Power calculations were performed using the function *popower*, from the R package Hmisc [29]. In the study, the odds ratio will be conditioned on the patients’ baseline DOSS score, as well as for the stratifying variables center and aspiration, which should provide further power compared to estimating a marginal odds ratio, as assumed in the power calculations. To account for a dropout rate of 20%, 168 patients will be recruited for each group.

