## Statistical methods

### Statistical methods for primary and secondary outcomes {27a}

The primary endpoint will be analyzed using an ordinal regression (proportional odds) model, adjusting for baseline DOSS [18, 19] as well as for the stratifying variables center and aspiration. The choice of using random or fixed effects for center is yet to be determined depending on the number of centers that will be recruited. A statistical analysis plan will be established before data retrieval, predetermining details on the analyses.

Further, nutritional status [23], swallowing-related quality of life [24], Barthel index [27], and mRS [28], all variables on ordinal scale, will be analyzed using ordinal regression, adjusted for baseline values, while group differences in the rate of aspiration pneumonia will be tested using negative binomial regression.

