### Interim analyses {28b}

An interim analysis is planned once 50% of participants have been assessed at end-of-treatment. At that point, an independent statistician will perform a blinded non-comparative sample size re-estimation. The updated sample size will be determined based on the observed marginal DOSS score distribution in the control group, targeting 90% power to detect a group difference at an odds ratio of 2.0, using the same sample size calculations as previously described. Because this re-estimation is non-comparative, it does not inflate the nominal type I error rate.

A second interim analysis will be conducted when 75% of the participants (according to sample size determined by the sample re-estimation) have completed the end-of-treatment assessment to evaluate efficacy. A group sequential design will be employed using the Lan-DeMets alpha-spending function with an O’Brien-Fleming type boundary. The primary ordinal regression analysis will be performed on the available data. The trial may be stopped early if the intervention shows overwhelming superiority, as determined by the boundary.

Strict operational safeguards regarding data access will be maintained throughout the study. Results of the interim analyses (both the sample size re-estimation and the efficacy calculation) will be known only to the independent statistician, while principal investigators and the study statistician will remain blinded to the results unless the independent statistician recommends stopping the trial.

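### The age interaction is to be tested with a split at 65 in a population expected to average 75, which discards about half or more of the information on a linear age trend; the sentence interpreting significant interactions should also be softened

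*Protocol article*

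**What the plan says.** The section on methods for additional analyses {27d} in the protocol article states the purpose as follows: "Pre-specified subgroup analyses will be conducted to evaluate the consistency of the treatment effect across key baseline characteristics". It then fixes the factors: "The defined subgroups include sex, age group (<65 vs. ≥65 years), stroke type (ischemic vs. hemorrhagic; supratentorial vs. infratentorial), and baseline severity of dysphagia". Each factor gets its own model ("we will fit separate ordinal regression models for each subgroup factor") with a treatment-by-subgroup interaction term, and the reading of the result is also fixed: "A significant interaction term will indicate a differential treatment effect across the subgroup categories".

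Table 1, on the expected characteristics of participants, describes adults aged 18 and above, "with mean age 75 based on age distribution in the Swedish National Stroke Registry". No SD of age is given. The article states no significance level for the interaction tests. It leaves details of the analyses to a statistical analysis plan that is not shown: "A statistical analysis plan will be established before data retrieval, predetermining details on the analyses".

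**The concern.** The age cut lies ten years below the centre of the population that the protocol itself expects. Two losses follow. Turning a measured continuous variable into two categories discards information wherever the cut is placed. Placing it far from the centre leaves one small group, which makes the comparison less precise still. If the effect of training rises or falls with age, the planned test has a poor chance of showing it, although age in years can be analysed at no extra cost.

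The second matter is smaller. Several interactions are tested separately, and the text says without qualification that a significant one will indicate a differential effect. A reader who follows that sentence literally would treat a single significant result out of four or five as established. The article expects the findings to bear on treatment guidelines, so a chance finding by sex, age or stroke type could receive more weight than it deserves.

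**Working it through.** **Inputs from the protocol article.** Sample size {19}: "135 subjects are sufficient to detect an odds ratio of 2 with 90% power using an ordinal proportional odds regression model", which must mean 135 per group because 168 per group are recruited to allow for 20% dropout; assumed DOSS distribution 3, 7, 10, 13, 24, 30 and 13%. Table 1: mean age 75. Section {27d}: cut at 65 and the list of factors.

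**Assumptions.** Two-sided 0.05; age approximately normal with SD 8 to 13 years; no covariate adjustment in the power figures.

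**1. The plan's own figure.** The sum of the cubed proportions is 0.0466, so the ordinal factor is 1 − 0.0466 = 0.9534. The proportional-odds formula gives a total of N = 12 × (1.960 + 1.282)² / (0.693² × 0.9534) ≈ 275, or about 138 per group. With 135 per group the information on the log odds ratio is

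V = 135 × 135 × 270 / (3 × 271²) × 0.9534 = 21.29,

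and power is Φ(0.693 × √21.29 − 1.96) = Φ(1.24) ≈ 89%. The stated 135 and 90% are reproduced closely, so the same V can be used for the interactions.

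**2. Share under 65.** f = Φ((65 − 75)/SD).
- SD 8: Φ(−1.25) = 10.6%, about 29 of 270 evaluable patients.
- SD 13: Φ(−0.77) = 22.1%, about 60 of 270.

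**3. Power for a ratio of odds ratios of 2.** The standard error of the log ratio is 1/√(V f(1 − f)).

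| Split | f(1 − f) | SE | 0.693/SE | Power |
|---|---|---|---|---|
| Even | 0.250 | 0.433 | 1.60 | 36% |
| Age 65, SD 13 | 0.172 | 0.522 | 1.33 | 26% |
| Age 65, SD 8 | 0.094 | 0.705 | 0.98 | 16% |

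**4. Information kept on a linear age interaction.** This is the squared correlation between the indicator and normally distributed age, φ(z)² / (f(1 − f)), where z is the cut in SD units.
- SD 8: 0.1826² / 0.0945 = 0.35.
- SD 13: 0.2968² / 0.1721 = 0.51.
- For comparison, a cut at the mean: 0.3989² / 0.25 = 0.64.

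So part of the loss comes from dichotomising at all and part from where the cut lies. In practical terms, suppose that the continuous test had 80% power against some linear trend. The split would have Φ(2.80 × √0.35 − 1.96) ≈ 38% at SD 8 and Φ(2.80 × √0.51 − 1.96) ≈ 52% at SD 13.

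**5. Chance of at least one significant interaction when none exists.** There are five tests if the two stroke-type splits are separate factors, and four if they are one.
- Five independent tests: 1 − 0.95⁵ = 22.6%.
- Four independent tests: 1 − 0.95⁴ = 18.5%.
- Five equally correlated tests, simulated: 21.8% at a correlation of 0.2 and 18.2% at 0.5.

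The range is about 18–23%.

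**The case against.** The plan does several things well. The subgroups are pre-specified, heterogeneity is judged by interaction terms and not by separate p-values within subgroups, and the tests stand among the additional analyses, apart from the primary conclusion. A cut at 65 contradicts nothing in Table 1, and an uneven split does not raise the false-positive rate of its test. The size of the loss depends on an SD that the document does not give, on normality and on a linear trend; if the effect really changed in a step at 65, the split would be the better test. The power figures are marginal, and the article expects covariate adjustment to add some power. All of this stands, and it limits the point to an inefficient choice. It does not remove it, because the cut is fixed in the protocol itself and the continuous alternative uses data already collected.

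On the wording, the significance level and any multiplicity rule may properly be in the analysis plan. That is a fair answer to a complaint that the tests are unadjusted: the article only states no adjustment. The sentence on interpretation nevertheless remains unqualified.

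A reader might also infer that the plan will take a non-significant interaction as proof of consistency. The text does not say so; it names consistency as the purpose and interprets only a significant term. Nor do the documents support saying that a Holm or similar adjustment is required. Statisticians differ on adjusting additional subgroup tests, and the analysis plan may settle it.

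**Conclusion.** The point holds as a matter of efficiency for age, with a minor wording point attached. For an assumed SD of 8–13 years and normal age, about 11–22% of patients are under 65, power for a ratio of odds ratios of 2 is about 16–26% against about 36% for an even split, and about 35–51% of the information on a linear age interaction is kept. The power figures rest on 135 per group, two-sided 0.05 and no covariate adjustment.

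The chance of at least one spurious significant interaction is about 18–23%, conditional on four or five tests at 0.05 and no true interaction. A figure of one in four is not reached under any of the cases examined. The type I error of the primary test and the primary conclusion are not affected.

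**What to change.** Test the treatment-by-age interaction in the ordinal model with age as a continuous variable, allowing for non-linearity if needed, and keep the under-65 and 65-or-older estimates for display. Replace the sentence on interpretation with one saying that the ratio of odds ratios is reported with its 95% CI for every factor, and that a significant interaction is exploratory and is read in light of the number of tests.

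The cost is a couple of sentences, in the protocol or in the analysis plan that is due before data retrieval, and very little programming. No new data are needed. The small downside is that a continuous term assumes a shape for the age trend, which a non-linear term relaxes at the price of some power.
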